### Health system-level outcomes

We shall assess the provision of integrated care from a health system perspective using the Assessment of Chronic Illness Care, which covers six areas of system change to promote optimal chronic care (linkages to community resources, self-management support, decision support, delivery system design, clinical information systems and organisation of the health system) [69]. We will complete the Assessment of Chronic Illness Care on a sample of clinic staff from intervention and control clinics at 12 months. In addition, we shall conduct qualitative process evaluation interviews with one facility manager and one service provider from each of the intervention clinics at 12 months to understand their perspectives on how integrating mental health services for depression has affected overall HIV clinical care.

### Participant recruitment and timelines

We will conduct clinic recruitment in two phases. We deem this phased approach necessary because of the scope of the intervention support and fieldwork operation required for the trial, both of which place considerable demands on the trial co-ordinating centre operating with limited human resources and a limited budget. The trial will start in the [name] district because the intervention has been piloted in that district and because the comparison intervention, the Integrated Care Services Model, has been implemented in the district before Bojanala because of its inclusion as one of the NHI pilot districts. We will conduct clinic randomisation on two separate occasions to allow for changes in clinic operation (smaller clinics are closed or relocated on a regular basis in South Africa) and the volume of attendances. We will factor in an embedding period of 2 months between the start of the intervention and recruitment of patient participants. In determining the duration of the embedding period, we balanced the time required to ensure the intervention was functioning within the clinics with the likelihood that patient participants had not yet been exposed to the intervention by the time of enrolment. Figure 3 shows the recruitment of clinics and patient participants into the trial as well as follow-up evaluations.

### Sample size

We calculated the sample size for a superiority trial because we hypothesized that the intervention would lead to reduced depressive symptoms for patients on ART with comorbid depression, which would in turn positively influence their adherence to ART and care, and improve their HIV outcomes. We based our estimates of viral load suppression on data from our previous RCT on task-shifting HIV care in which 70% of ART patients had suppressed viral loads at follow-up with an intra-clinic correlation coefficient (ICC) of 0.046 [40]. We assumed that rates of viral load suppression will be slightly lower in a group of patients suffering from depression (65%) as it is a known risk factor for poor adherence [18, 70]. A sample size of 2000 participants from 40 clinics (50 patients per clinic, 1000 per group) provides 80% power to detect a 10% difference in 1-year viral load suppression at the 5% significance level assuming an ICC of 0.04 and a 20% loss to follow-up based on a previous trial in this setting [38]. To determine the appropriate parameters for the PHQ-9 sample size calculation we searched PubMed for all RCTs which had used the PHQ-9 as an outcome. Of the 126 trials screened, we identified nine as relevant to the design of our trial [71–79], including four cluster trials and five individually randomised studies. The trials used a mix of metrics, including difference in means, response and remission rates, measured at a range of time points. We disregarded several of the trials because their baseline scores were far higher than those we had observed in our population of interest during the validation of the Setswana localisation of the PHQ-9. We instead based our sample size estimates on three cluster trials completed in the Netherlands [71], Italy [77] and the UK [79], where PHQ-9 response rates at 6 months were reported and where baseline scores were similar to what we anticipated. Only two of the five cluster trials reported an ICC [71, 79] and, in one of these, it was uninterpretable because of very small cluster sizes [71]. We then completed a series of calculations to determine power to detect a difference of between 10% and 12% in response rates at 6 months, with the number of clusters and cluster size fixed by the viral load calculation at 40 and 50, respectively (Table 6). We allowed for the proportion of those who responded in the control group to vary between 30% and 35%, for the ICC to vary between 0.02 and 0.04 (we assumed lower ICCs were likely given that the PHQ-9 is a health outcome) and for a loss to follow-up rate of 20%. This showed that a sample of 50 patients in 40 clusters (1000 per group) yielded a power of between 73% and 96% to detect a difference of between 10% and 12% in response rates at 6 months.

**Table 6 Tab6:** Power calculations for primary PHQ-9 outcome (response rate at 6 months defined as 50% improvement from baseline)

No. of clusters per group	Cluster size	Proportion responded in control group	Proportion responded in intervention group	Alpha	ICC	Power (No dropout)	Power (20% dropout)
20	50	0.30	0.40	0.05	0.04	76	73
20	50	0.30	0.40	0.05	0.02	90	87
20	50	0.30	0.42	0.05	0.04	89	87
20	50	0.30	0.42	0.05	0.02	97	96
20	50	0.35	0.45	0.05	0.02	89	87
20	50	0.35	0.47	0.05	0.02	97	95

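### The 73% to 96% power range for PHQ-9 response leaves out the least favourable case within its own stated inputs; the lower end is about 70%, and one Table 6 cell appears too high

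*Protocol article*

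**What the plan says.** The Sample size section takes the number of clinics and the cluster size from the viral load outcome and then examines power for PHQ-9 response at 6 months, "with the number of clusters and cluster size fixed by the viral load calculation at 40 and 50, respectively (Table 6"). The difference of interest is 10 to 12 percentage points. The text allows the response proportion in the "control group to vary between 30% and 35%, for the ICC to vary between 0.02 and 0.04", and assumes 20% loss to follow-up. It concludes that the sample "yielded a power of between 73% and 96% to detect a difference of between 10% and 12% in response rates at 6 months".

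Table 6 has six rows. Four have a 30% control rate (v 40% and v 42%, each at ICC 0.04 and 0.02). Two have a 35% control rate (v 45% and v 47%), both at ICC 0.02 only. The 73% comes from the first row, "20 50 0.30 0.40 0.05 0.04 76 73", and the 96% from 30% v 42% at ICC 0.02.

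**The concern.** Two control rates, two ICCs and two differences make eight corner combinations, and Table 6 holds six. The two absent ones pair the 35% control rate with ICC 0.04, and one of them (35% v 45%) is the worst case for power. The sentence presents 73% as the lower end over the stated input ranges, when it is only the lowest value among the rows shown.

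PHQ-9 response is a co-primary outcome whose power was not designed for directly, so this range is the only assurance the article gives for it. A reader judging the planned sensitivity of the trial, for instance after a null result, would take the lower end at face value. The high-ICC corner also deserves to be shown because the ICC evidence was thin: the section says that only two of the trials reported an ICC and that one of these could not be interpreted.

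Separately, Table 6 prints 87% with dropout for both 30% v 40% and 35% v 45% at ICC 0.02. These two cases should not give the same integer.

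**Working it through.** **Inputs** (Sample size section and Table 6): 20 clinics per group; m = 50 patients per clinic, or 40 after 20% loss; alpha 0.05, taken as two-sided because the article does not say; ICC 0.02 or 0.04; control response 30% or 35%; difference 10 or 12 points.

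**Which case is worst, without choosing a formula.** At the same difference and ICC, power falls as the summed binomial variance rises:

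- 30% v 40%: 0.30×0.70 + 0.40×0.60 = 0.210 + 0.240 = 0.450
- 35% v 45%: 0.35×0.65 + 0.45×0.55 = 0.2275 + 0.2475 = 0.475

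So 35% v 45% at ICC 0.04 has less power than 30% v 40% at ICC 0.04, the case printed as 73%.

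**Formula used for size.** The article names no method for Table 6. The following one fits it best:

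- design effect DE = 1 + (m − 1) × ICC
- SE = √[(p1q1 + p2q2) × DE / (20m)]
- power = T38(d/SE − 2.024), where T38 is the t distribution function with 2×(20 − 1) = 38 df and 2.024 is its 97.5% point

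**Reproducing the printed 73%** (30% v 40%, ICC 0.04, m = 40): DE = 1 + 39×0.04 = 2.56; SE = √(0.450×2.56/800) = 0.03795; d/SE = 2.635; power = 72.8%.

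**Omitted worst case** (35% v 45%, ICC 0.04, m = 40): SE = √(0.475×2.56/800) = 0.03899; d/SE = 2.565; power = 70.4%.

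**All rows (power, %):**

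| Control v intervention | ICC | Printed: no dropout / 20% | Computed: no dropout / 20% |
|---|---|---|---|
| 30 v 40 | 0.04 | 76 / 73 | 76.1 / 72.8 |
| 30 v 40 | 0.02 | 90 / 87 | 90.4 / 86.8 |
| 30 v 42 | 0.04 | 89 / 87 | 89.1 / 86.6 |
| 30 v 42 | 0.02 | 97 / 96 | 97.2 / 95.6 |
| 35 v 45 | 0.02 | 89 / **87** | 88.8 / **85.0** |
| 35 v 47 | 0.02 | 97 / 95 | 96.6 / 94.7 |
| 35 v 45 | 0.04 | not shown | 73.8 / 70.4 |
| 35 v 47 | 0.04 | not shown | 87.5 / 84.9 |

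Eleven of the twelve printed cells agree to the integer, including both ends of the quoted range. A noncentral t calculation changes nothing of substance: it gives 73.9 / 70.5 for the first omitted row and the same 85.0 for the cell printed as 87.

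**Does a normal approximation rescue the text?** For the omitted worst case with dropout, z gives 72.4% (pooled variance) or 72.7% (unpooled). The same formulas give 74.7% or 75.0% for the cell printed as 73, so they are not what produced the table.

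**The cell printed as 87.** With 20% dropout at ICC 0.02, 30% v 40% and 35% v 45% give:

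- t: 86.8 v 85.0
- unpooled z: 88.5 v 86.8
- pooled z: 88.3 v 86.6

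The gap is 1.7 to 1.8 points each time. Two values that round to the same integer differ by at most 1 point, so none of these formulas yields 87 for both. The 35% v 45% cell is the one that departs from the method fitting the rest.

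**The case against.** The strongest reply is that the range does summarise Table 6 correctly: 73 and 96 are the smallest and largest values in its dropout column, and the text never claims that every combination was run. The authors also explain why they expected the ICC to be low. On that reading the defect is loose wording, not a miscalculated bound. This has some force, and confining the sentence to the tabulated scenarios would make it true. As written, though, it lists the input ranges and then gives a power range for them, and a reader will take the lower figure as the floor.

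Three further points stand in part:

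- The 70% depends on a method inferred from the table, so it should be given as about 70%. That 73% is not the minimum does not depend on the method.
- The 87 v 85 discrepancy is about 2 points, is not an end of the range, and would be weak evidence alone, since z gives 86.6 to 86.8 for that cell. It is a secondary point that rests on consistency with the other eleven cells.
- The consequence is modest. The sample size was fixed by viral load, power below 80% is already disclosed, a null result would be judged mainly by its confidence interval, and follow-up is complete in one district and in progress in the other.

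The ICC of 0.046 quoted from the earlier trial is for viral load and lies outside the range stated for PHQ-9, so it is not used here.

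**Conclusion.** The point holds. Over the ranges the article states, power with 20% loss runs from about 70% to 96%, not from 73%. The overstatement at the lower end is roughly 2.5 points (72.8 − 70.4 = 2.4 before rounding). The direction follows from the binomial variances alone. The size assumes a two-sided 5% test, 40 patients retained in each of 20 clinics per group, equal cluster sizes and the t-based method that matches the rest of Table 6. On the same basis, the 35% v 45%, ICC 0.02 cell with dropout should read 85, not 87. This is a reporting error in the plan's favour on a co-primary outcome. It does not call the sample size into question.

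**What to change.** Rerun Table 6 with the software originally used and name the method. Then:

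1. Add the two missing rows at ICC 0.04. On the method above they are 0.35 v 0.45 (74 without dropout, 70 with) and 0.35 v 0.47 (88 and 85).
2. Check the 35% v 45%, ICC 0.02 cell with dropout and correct 87 to 85 unless the rerun shows otherwise.
3. Restate the range in the text as about 70% to 96%.

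If the rows are not added, the minimum is to say that the range covers only the scenarios tabulated and that 35% control response with ICC 0.04 was not among them.

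The cost is two table rows, one cell and one number in the text. Design, recruitment and analysis are unaffected; the stated lower end simply becomes less favourable.

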### Recruitment and data collection

We conducted clinic recruitment in two phases. We obtained an updated list of clinics in each district with recent headcount data. We scrutinized the GPS co-ordinates of the clinics to identify any clinics that might be located next to each other and thus be at risk of contamination. We then forwarded a cleaned-up list of eligible clinics to the statistician, who selected the largest facilities and completed randomisation within sub-district strata. Because clinics in South Africa sometimes close or are amalgamated with others, we repeated the process for the Bojanala clinics a few months before starting work in that district. We split clinic recruitment evenly between the two districts with 20 clinics from each.

Patient recruitment occurred independently of clinical care or participation in the group psychosocial intervention for depression. We adopted a pragmatic approach, enrolling all patients who met the eligibility criteria regardless of exposure to the intervention, recognising that the detection of mental disorders and linkages to care are pressing challenges for integration of mental health services into primary care and that failure to account for this in the design of the trial would limit the generalisability of its findings to real-world primary care settings. Patient participant recruitment started approximately 2 months after the training of nurses and counsellors in the intervention clinics. Trained fieldworkers invited, screened and enrolled patient participants in the trial using a three-stage process as outlined in Additional file 4. First, trained fieldwork recruiters explained the study to patients in the waiting room, inviting those attending for chronic care services to come forward for more information if they were interested. Depression, HIV or ART were not be mentioned during this general information sharing so as not to single out those who wished to participate. The recruiter completed a brief verbal screen of patients who came forward to establish whether or not they were on ART and whether they planned to stay in the study area for the duration of the following year; this was done on a one-to-one basis. Eligible patients were then walked across to a fieldwork interviewer based in a private section of the clinic where the emotional content of the PHQ-9 instrument was explained and opt out consent sought before proceeding with the full screen. We then sought formal consent from patients who screened positive using the PHQ-9. This covered permission to be interviewed at enrolment, at the two subsequent time points, 6 and 12 months later, determination of the participant’s viral load at enrolment and 12 months later, permission to review their clinical folders and hospital records to assess quality of care provided and healthcare utilisation, and to send reminders and confirmation of follow-up interviews by text message and phone calls. We requested participants to supply their national identity numbers to permit linkage with the national population register, which records more than 90% of all deaths in South Africa. We only collected patient identifiers once written informed consent was provided (Additional file 5). The recruitment process for the PRIME and CobALT trials was conducted as a combined process in the [name] district and patient recruitment continued until the target of 50 patients per clinic was met for both trials. We invited patients who were on both ART and antihypertensive medications, and who qualified for enrolment in the trial, to participate in both studies and complete two sets of consent forms. Fieldwork interviewers conduct interviews in one of the three local languages (Setswana, English, Afrikaans), chosen by the participant (see Additional file 6 for the full questionnaire). Fieldwork interviewers collect data using handheld electronic devices, which we have previously used in similar field work data collection exercises in South Africa [80]. We ask participants to return to the clinic for follow-up interviews. We send text reminders in advance of follow-up visits, and contact participants by telephone to confirm their appointments. At follow-up, participants undergo an interview to determine the severity of their depressive symptoms, the nature of the care they received at the clinic, including care for depression and HIV, and other healthcare utilisation and economic outcomes. Follow-up viral loads will be drawn from all patients at 12 months.

### Randomisation, allocation concealment and blinding

We randomised clinics and their patients to one of two parallel groups, with an allocation ratio of 1:1. Within each district, we considered the distribution of clinics within sub-districts to ensure that we did not introduce potential confounding through geographically determined management of clinics. Within the [name] district, 12 clinics fall within the Matlosana sub-district in the area, including and surrounding the major town of Klerksdorp, and have been randomised as one stratum. The remaining eight clinics are situated in more rural areas and randomised together. Within the Bojanala district, 10 clinics are in the central district of Rustenburg in and around the town of the same name and are randomised in a 1:1 allocation. The remaining 10 clinics are distributed over a far wider area than in [name] district and spread across the three sub-districts of Moretele, Kgetleng River and Madibeng. We combined two of the smaller sub-districts (Moretele and Kgetleng River) into one, so that we have two strata each with five clinics available for randomisation. We randomly selected one of these strata to have three intervention clinics to two control clinics, and vice versa in the other stratum, so that we have 10 intervention clinics and 10 control clinics in the Bojanala district. The trial statistician carried out randomisation using n-Query advisor prior to the intervention or screening of participants for recruitment. Blinding of participants and clinicians is not possible because it will be clear which clinics will be implementing what interventions. The trial statistician who carried out randomisation did not know the characteristics of the clinics being randomised, and the primary statistical analysis will also be blinded to allocation status.

### Data management

Interview data is uploaded as soon as questionnaires are completed, internet connectivity permitting, and stored in a secure SQL server at the Trial Co-ordinating Centre at the University of Cape Town Lung Institute. We integrate data from interviews with those from other sources to create a longitudinal record for every patient participant (Fig. 5). These other sources include blood results for the viral load samples drawn as part of the research process as well as routinely monitored viral loads which are collated in a central national repository. We search hospitalisation records quarterly and integrate linkages into the research dataset. We maintain a separate database of patients referred to facility-based counsellors and link their attendance of sessions with the trial patient database. The research version of the national population register, curated by the South African Medical Research Council, will be linked once at the end of the study to identify any deaths which had not already been identified through follow-up of patients who did not return for their 6- and 12-month interviews.

**Fig. 5 Fig5:**
[figure not shown]
Integration of data sources into a longitudinal patient record

Quality control measures include supervision of fieldworkers, electronic alert messages for fieldworkers if unusually high or low values are entered into the electronic questionnaire, automated skips, and monitoring of the data to identify unusual values or trends. The handheld devices used for data collection are password protected and interview data is uploaded at the end of each interview without being stored on the device. Only a small number of data managers have access to personal identifiers. Anonymised data (without names or national identity numbers) will only be provided to selected members of the research team. Members of the research team, including all fieldworkers and fieldwork supervisors, are required to sign a confidentiality agreement to ensure the protection of confidential data.

### Statistical methods

We will estimate the effects of the intervention by comparing the outcomes of intervention and control group patients using multiple mixed effects regression models, with clinics as a random effect to account for the intra-cluster correlation of outcomes. We will include the stratum as a covariate in the regression models, and will use Stata statistical software for the analysis. All clinics and patients will be analysed in the treatment group to which they were randomly assigned. We will ascertain the completeness of follow-up by group to evaluate the integrity of the planned analysis. We will use binomial regression to estimate differences in proportions of patients with suppressed viral loads and who have responded in terms of their depressive symptoms, measured using the PHQ-9. We will analyse secondary outcomes as follows: binomial regression for binary outcomes, linear regression for changes in depression scores, blood pressure, weight, and waist circumference by comparing values at follow-up adjusted for baseline values, and Poisson regression for count outcomes such as clinic visits and inpatient days, accounting for individuals’ duration of follow-up.

Planned secondary analyses include analysis of primary outcomes stratified and adjusted for treatment severity, treatment status and comorbidities at baseline. We will also explore whether there is a differential effect among those patients who reported receiving the counselling intervention.

The economic evaluation will include descriptive statistics describing the health system and societal costs of living with HIV and depression, a cost effectiveness analysis, and modelling of the intervention beyond the timeframe of the study.

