## Methods

### Trial design

CobALT is a pragmatic, two-arm, parallel group, stratified and cluster randomised, superiority trial set in two health districts of the North West Province of South Africa. It is a type 2 hybrid design [48], evaluating an implementation strategy comprising clinical, educational and organisational elements (Table 3) in a coherent programme designed in collaboration with operational managers and health providers [42]. It combines characteristics of implementation (e.g. process evaluation and quality of care indicators) and clinical effectiveness research (e.g. primary health outcomes). We randomised primary healthcare clinics with a 1:1 allocation ratio, and will measure outcomes on individual patients. The trial is being implemented in two phases. The site for phase 1 is the [name] district (20 clinics, 1000 patients), where the intervention started in 10 clinics in April 2015 and patient recruitment commenced in April 2015. We are conducting phase 2 in the adjacent Bojanala district (20 clinics, 1000 patients), where the intervention started in 10 clinics in April 2016 and patient recruitment commenced in July 2016.

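### Secondary analyses of both co-primary outcomes condition on baseline treatment status, which is recorded after the intervention has started and may already be affected by it

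*Protocol article*

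**What the plan says.** The main model in Statistical methods is a mixed effects regression with clinic as a random effect and stratum as a covariate. The section then adds, as planned secondary analyses, "analysis of primary outcomes stratified and adjusted for treatment severity, treatment status and comorbidities at baseline". It does not say which treatment is meant.

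The order of events is set out elsewhere in the protocol article:

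- Randomisation, allocation concealment and blinding: clinics are allocated before the intervention starts and before patients are screened.
- Participant recruitment and timelines: there is to be an "embedding period of 2 months between the start of the intervention and recruitment of patient participants". Its length was weighed against "the likelihood that patient participants had not yet been exposed to the intervention by the time of enrolment".
- Recruitment and data collection: the pragmatic approach meant "enrolling all patients who met the eligibility criteria regardless of exposure to the intervention". The same section reports: "Patient participant recruitment started approximately 2 months after the training of nurses and counsellors in the intervention clinics".
- Trial design, phase 1: "the intervention started in 10 clinics in April 2015 and patient recruitment commenced in April 2015". Phase 2: "the intervention started in 10 clinics in April 2016 and patient recruitment commenced in July 2016".

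**The concern.** In an individually randomised trial, baseline values precede allocation, so stratifying on them or adjusting for them is safe. Here the patient's baseline interview follows both the randomisation of the clinic and the start of the intervention. Depression treatment is the variable most exposed to this, because the intervention works by detecting depression and moving patients into counselling or medication.

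If some intervention-clinic patients are treated at baseline because of the intervention, two things follow. First, the treated and untreated strata hold different kinds of patients in the two arms, so a within-stratum comparison is no longer a like-for-like randomised one. Second, any benefit that flows through treatment begun before enrolment is adjusted away. At stake is whether these results for PHQ-9 response at 6 months and viral load suppression at 12 months can be read as baseline-adjusted effects.

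**Working it through.** **1. The plan's own figure: the 2-month gap.** Using the Trial design dates:

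- Phase 1: intervention April 2015, recruitment April 2015. The longest possible gap is 1 to 30 April, or 29 days. Two months is not reproduced. Table 1 also starts fieldwork in April 2015.
- Phase 2: intervention April 2016, recruitment July 2016. The shortest gap is 30 April to 1 July: 31 + 30 + 1 = 62 days. The longest is 1 April to 31 July: 29 + 31 + 30 + 31 = 121 days. The nominal gap is 3 months, and about 2 months is possible only at the lower edge.

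**2. Can the intervention change baseline treatment status?**

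- Table 3 trains intervention-clinic nurses to detect depression and refer to counsellors or a doctor.
- The Intervention arm section places counsellors in those clinics.
- Table 4 lists antidepressant treatment and counselling as secondary outcomes, both also measured at baseline.

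The trial therefore treats depression treatment as something the intervention should move, and it records the baseline value after the intervention has begun.

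**3. How much of the treated stratum could be there because of the intervention?** Let c be the share treated at baseline without the intervention and x the extra share it adds. The fraction is x/(c + x). The documents give no x; 5 and 15 points are assumed. For c, the Background reports an earlier trial in another province with 294/2466 = 12% on antidepressants and 614/2466 = 25% on any treatment.

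- c = 12%: 5/17 = 29% to 15/27 = 56%.
- c = 25%: 5/30 = 17% to 15/40 = 38%.

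These figures describe who is in the stratum. They do not measure bias.

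**4. An illustration of bias.** All inputs are assumed:

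- Half the patients are more severe.
- Control response is 40% in milder and 20% in more severe patients.
- In control clinics 5% of milder and 19% of more severe patients are treated at baseline (12% overall).
- An average rise of a in the intervention arm adds 0.5a in milder and 1.5a in more severe patients.
- The true effect is 10 points in everyone.

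Within a stratum, response is the sum over severity of (0.5 × probability of being in that stratum × response), divided by the sum of (0.5 × probability).

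Untreated stratum, a = 10 points:

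- Control: (0.475 × 0.40 + 0.405 × 0.20)/0.88 = 30.8%.
- Intervention before any effect: (0.45 × 0.40 + 0.33 × 0.20)/0.78 = 31.5%.
- The spurious difference is 0.7 points, so the estimate is 10.7.

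| Rise in baseline treatment (points) | Estimated effect, untreated | Estimated effect, treated |
|---|---|---|
| 0 | 10.0 | 10.0 |
| 5 | 10.3 | 10.2 |
| 10 | 10.7 | 10.4 |
| 20 | 11.7 | 10.5 |
| 30 | 13.0 | 10.6 |

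If the extra treatment fell mainly on milder patients, the untreated estimate would move the other way. Effect lost through treatment begun before baseline is not in this model and would pull estimates down.

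**The case against.** The strongest reply is that these are labelled secondary analyses. That stands: the main model does not contain treatment status. A reader might infer that the trial's main estimates of the co-primary outcomes are biased by this adjustment; the documents do not support that.

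Second, the term is undefined. ART yes or no cannot vary, since every participant is on ART, but ART regimen is recorded at baseline and is another possible meaning. Depression treatment is the likelier reading, not the only one, so the point is conditional on it.

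Third, prior exposure is allowed but not shown, and the embedding period was chosen with that risk in mind. This also stands. A reader might infer that baseline treatment was changed; the documents show only that it could have been.

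Fourth, on dates, Recruitment and data collection counts from training, not from intervention start, so it need not contradict Trial design, and phase 2 could be just over 2 months. What survives is the phase 1 conflict between Trial design and Participant recruitment and timelines. It would be too strong to say that all 1000 phase 1 patients had no embedding period: April 2015 is when recruitment began, and later enrolees had a longer lead-in. If the April dates are right, the conditioning problem is weaker for early phase 1 patients.

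Differing exposure between districts does not by itself bias the overall comparison, because randomisation is within district strata and stratum is in the model.

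**Conclusion.** The point holds in a limited form. If treatment status means depression treatment, the planned stratified and adjusted secondary analyses condition on a variable recorded after randomisation and after the intervention began, which the intervention is designed to change. Those estimates may be biased, in a direction that cannot be fixed in advance.

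On the assumed inputs the selection part is modest: 0.3 to 1.7 points on a 10-point effect in the untreated stratum for a 5- to 20-point rise in baseline treatment. It is nil if baseline treatment is unaffected. The loss of effect through early treatment is unquantified.

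Baseline severity and diagnosed comorbidities share the caveat to a lesser degree, since the intervention also targets symptoms and the diagnosis of comorbid illness is itself an outcome in Table 4. The phase 1 date conflict is a separate, definite inconsistency.

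**What to change.** - Drop baseline depression-treatment status from the stratification and adjustment set. Alternatively, define it as depression treatment begun before the clinic's intervention start date, taken from clinical folders and linked records. Control clinics have no such date, so use the start date of the same phase. The folders, which participants consent to have reviewed, would have to carry the definition in both arms; the counsellor database can date counselling only after counsellors were in place.
- State in the analysis plan which treatment is meant.
- Report baseline depression treatment, severity and diagnosed comorbidities by arm, and note that analyses using severity and comorbidities carry the same caveat to a lesser degree.
- Reconcile the phase 1 dates in Trial design with the 2-month embedding period in Participant recruitment and timelines. A re-dated treatment variable depends on the right start date.

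The cost is a change of analysis-plan wording, a date correction and some folder abstraction if the variable is re-dated. The downside is one fewer exploratory subgroup, or a less complete one where treatment start cannot be dated. The main analysis does not change.
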